The app is accessed with a unique individual code on the participant’s own smartphone. Once the app is installed, participants can begin with 0Phobia intervention which they can follow for 3 weeks at their own pace. During this 3-week period participants receive weekly motivational emails with information reminding them to start or continue with 0Phobia to increase intervention adherence. These emails will be sent unconditional of app activity.

If participants have questions or experience severe distress, they are encouraged to contact the research team.

After module 6, participants are encouraged to seek out heights in real life. Therefore, participants who finish 0Phobia who have finished module 6 earlier than the 3 weeks will receive an email with a link to the Acrophobia Questionnaire (AQ [28]) in order to obtain estimates of the treatment on levels of acrophobia through VR exposure.

Directly following the conclusion of 0Phobia, participants are sent a link to the online post test. After completing the post test, the waitlist condition will be granted access to the 0Phobia therapy. After 3 months, participants in the experimental condition are asked to fill in the follow-up questionnaire.

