### Sample size

The primary outcome measure, the AQ, has been used for the power calculations. In previous RCTs using the AQ as an outcome measure, effect sizes of 0.79–1.42 [14, 15] were demonstrated. However, as the present intervention will use low-end cardboard VR goggles instead of expensive head-mounted displays, the current study uses a more conservative estimate for the post-treatment effect on the AQ. In order to detect a difference between the experimental and the waitlist control condition with a standardized effect size (Cohen’s d) of 0.50 (two-sided), an alpha of 0.05 and statistical power (1 − *β*) of 0.80, we need 64 participants in each condition (128 participants in total). With an anticipated dropout of 40%, this requires a total target sample size of 180 participants.

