### Analyses

#### Statistical analyses

The primary outcome measure (AQ; [28]) and secondary study parameters (ATHQ, PHQ, IPQ, SUS, BAI, and Pearlin Mastery Scale) will be treated as continuous outcomes. Continuous variables will be presented as mean, standard deviation, and minimum and maximum number of observations. Categorical variables will be presented in terms of frequencies and percentages. Descriptive statistics of demographics and clinical outcomes will be compared between the experimental and the waitlist condition.

To assess whether attrition is non-random, we will construct a balancing table for background characteristics, pre-scores and other covariates in which participants with and without missing outcome observations are compared. Potential implications of non-random sample attrition on the observed treatment estimates will then be assessed by estimating treatment effect bounds for samples with non-random sample selection/attrition as proposed by Lee [47]. Using this approach we are able to infer whether observed differences between the intervention and control groups can be explained by extreme, non-random sample selection. Depending on these results, missing outcome observations for participants will be imputed based on pre-scores and a set of background characteristics. The quantitative analysis of the primary and secondary endpoints will be performed on an intention-to-treat (ITT) basis following the per-protocol analysis. The primary analysis will be based on ITT. Potential dependency between outcome measures is addressed using multivariate analyses. Potential heterogeneity will be addressed by estimating treatment effects for subgroups (e.g., based on pre-scores). In order to understand the mechanisms by which observed differences are generated, a rich set of analyses is performed based on variation in (1) experiences when using the app (e.g., perceived user friendliness, ecological momentary assessment, cybersickness, VR vs 360°) and (2) intensity of using the app. Per-protocol analysis will be based on two groups: (1) those who returned the post-test and follow-up questionnaires (completers) and (2) those who completed 50% or more of the treatment modules and returned the questionnaires (adherent completers). Comparisons will be made between and within the groups before and after measurements.

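### Whether the primary ITT analysis imputes is decided after seeing the trial's own results, and Lee bounds are not the safeguard claimed when attrition is similar in both arms

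*Protocol article*

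**What the plan says.** The Statistical analyses section of the protocol article sets out a sequence.

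1. A table compares participants with and without missing outcomes on baseline variables.
2. Lee's treatment effect bounds are then estimated. The article says that with them "we are able to infer whether observed differences between the intervention and control groups can be explained by extreme, non-random sample selection".
3. Imputation follows conditionally: "Depending on these results, missing outcome observations for participants will be imputed", using pre-scores and background characteristics.

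The same section makes ITT the primary analysis. It gives no threshold for imputing and does not name the estimator to be used if imputation is not done. The next paragraph adds that app usage data will serve to model missingness. That is a different set of variables, and the waitlist arm cannot generate it before the post test.

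The Sample size section shows how much data this governs: "With an anticipated dropout of 40%, this requires a total target sample size of 180 participants". The Procedure section gives the arms different reasons to return the questionnaire: "After completing the post test, the waitlist condition will be granted access to the 0Phobia therapy".

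**The concern.** There are two linked problems.

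**The estimator depends on the result.** Lee bounds are computed from outcomes by arm. A rule that imputes or not after seeing them lets the trial's own treatment difference influence which estimate becomes primary. An analysis plan could add a threshold, but the article has already fixed a data-dependent choice. This is therefore more than a detail left for later.

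**The check lacks the property claimed for it.** Lee bounds rest on monotonicity: treatment may make people more likely to stay, or less likely, but not some of each. They trim the better-retained arm by the excess retention and nothing more. If both arms lose similar fractions, almost nothing is trimmed, however selective the losses are. If the app arm lost its most fearful members while the waitlist lost its least fearful, the two biases would add up, and the bounds could sit tightly around a wrong answer.

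**Working it through.** **The plan's own figures.** For d = 0.50, two-sided alpha 0.05 and power 0.80, the t-test needs 63.8, so 64 per arm and 128 in total, as stated. The target follows from 128 × 1.4 = 179.2, rounded up to 180. A 40% loss from 90 per arm leaves 90 × 0.6 = 54, which is used below. (Whether 180 is enough at that loss is a separate matter.)

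**Assumptions not in the article.** True effect zero; opposite selection (app arm loses high scorers, waitlist loses low scorers); pre-post correlation 0.6; the selection strengths shown. The article gives one dropout figure and no pattern by arm. Differences are app minus waitlist, in SD units.

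**A. Cost of the conditional choice alone.** Simulation with 90 per arm, 40% missing at random, 4,000 trials: complete-case rejects in 5.1% and pre-score-adjusted regression (a stand-in for imputation on pre-scores) in 4.8%. At least one of the two is significant in 7.8%, which is the ceiling if the choice follows the result.

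**B. Opposite selection through the pre-score** (log-odds 0.5 per SD, 40% missing per arm). Complete-case bias is −0.23 SD and it rejects in 22%. The adjusted analysis is unbiased and rejects in 4.6%. Large-sample Lee bounds are about [−0.24, −0.22], and the pooled missing-versus-observed pre-score difference is about 0.00. Here the decision to impute settles the answer, and neither the bounds nor a pooled table prompts it.

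**C. Opposite selection on the unobserved post-test score.** If dropout propensity has correlation b with the score and retention is r, the retained mean shifts by b × φ(z_r)/r in each arm. For r = 0.6, φ(z_r)/r = 0.386/0.6 = 0.644.

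- b = 0.2: bias 2 × 0.2 × 0.644 = 0.26 SD
- b = 0.3: bias 2 × 0.3 × 0.644 = 0.39 SD

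At 54 per arm the standard error is √(2/54) = 0.192, and false rejection is about 26–27% and 51–53%. Imputation within arm on the pre-score still leaves about 0.17 and 0.26 SD, and pre-score adjustment still rejects in about 18–19% and 37%.

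The log-odds version (40% missing per arm, large sample) shows the collapse of the bounds:

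| Log-odds per SD | Complete-case | Lee bounds | Pre-score-adjusted | Pooled pre-score difference | By arm (app / waitlist) |
|---|---|---|---|---|---|
| 0.25 | −0.20 | [−0.21, −0.19] | −0.13 | 0.00 | −0.15 / +0.15 |
| 0.5 | −0.38 | [−0.39, −0.38] | −0.25 | 0.00 | −0.29 / +0.28 |
| 1.0 | −0.66 | [−0.67, −0.66] | −0.45 | 0.00 | −0.50 / +0.50 |

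With 90 per arm, chance differences in retention give the bounds a median width of about 0.30 SD at log-odds 0.5. They still exclude the true zero in 85% of trials, against 45% when losses are random (bounds taken without confidence intervals).

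**D. Unequal attrition.** At 40% (app) versus 20% (waitlist) the trimmed share is (0.8 − 0.6)/0.8 = 0.25, which moves the trimmed mean by about 0.42 SD either way. Under the selection in C the bounds are about [−0.62, +0.22] for b = 0.2 and [−0.71, +0.12] for b = 0.3. Both contain zero. At 45% versus 35% and b = 0.3, the complete-case difference is −0.3 × (0.720 + 0.570) = −0.39, the trimmed share is 0.10/0.65 = 0.154, and the shift is about 0.28. The bounds, about [−0.67, −0.11], miss zero.

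**The case against.** Several points on the other side stand.

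- **The large rejection rates are not the price of the conditional wording.** A reader might infer that deleting the condition would remove the 26–53% false rejection in C. It would not. That bias comes from selection on the unobserved score, and about two thirds of it survives imputation on pre-scores, because such imputation assumes missing at random. The conditional choice alone costs at most about 7–8% against 5%.
- **The waitlist incentive does not by itself produce balanced, opposite attrition.** If access to the app keeps waitlist members in the study, their attrition should be lower. Retention is then unequal and the bounds widen, as in D. The collapse needs similar attrition in both arms, which the article neither predicts nor rules out.
- **The table does not use outcome values.** It uses baseline data and the fact of missingness; only the Lee bounds use outcomes. The article also does not say that the table is pooled. Split by arm, it could reveal opposite selection that is visible at baseline.
- **Complete-case is not named as the fallback.** The article places completers under the per-protocol analyses. That the ITT estimate would be complete-case without imputation is an inference.
- **A chance-flag rate for the table cannot be computed.** The article states neither the number of covariates nor a significance test for it.

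What these points leave untouched is the condition itself and the claim made for the bounds.

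**Conclusion.** The point holds in a limited form. The article makes imputation in its primary analysis depend on results that include the arm difference, with no rule. It also credits Lee bounds with excluding extreme selection, which they cannot do when attrition is similar between arms and opposite in kind.

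The size depends on assumptions that the article cannot confirm. It ranges from a few points of type I error when losses are random to a result decided by the choice of estimator when opposite selection runs through the pre-score (B). The bias in C shows why the bounds should not be read as reassurance; it does not measure the harm of the conditional rule. The documents do not support a claim that the trial will be biased without warning. With clearly unequal attrition the bounds warn, and a table by arm could too. At 40% anticipated dropout the matter is still worth settling before outcomes are analysed.

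**What to change.** - Remove the condition on imputation. Fix one primary ITT estimator for all 180 randomised, whatever the checks show: either multiple imputation within arm including baseline AQ, or a likelihood-based mixed model with baseline AQ.
- Keep complete-case and Lee bounds as sensitivity analyses. State the monotonicity assumption and drop the claim about extreme selection.
- Present the missing-versus-observed table separately by arm.
- Because the primary analysis would still assume missing at random, add a delta-adjusted sensitivity analysis that shifts imputed AQ values separately in each arm.

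The cost is wording and a few more analysis runs. The sponsor gives up choosing the estimator after seeing the data.

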### Randomization, blinding, and treatment allocation

A randomization list will be created with Random Allocation Software using block randomization of 6, 8, 10, and 12 blocks at an allocation ratio 1:1. Participants will be randomized into two groups: experimental or waitlist condition. The randomization list is kept by an independent researcher. This person reveals the next randomization outcome after every inclusion and thus ensures that the researchers are blind for treatment allocation. Due to the nature of the study, it is not possible to blind the participants for the randomization outcome.

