Intention-to-treat and per-protocol analysis will be used on continuous scales using regression estimation standardized effect sizes (Cohen’s *d*) and confidence intervals will be calculated. Usage data through the mobile app (anxiety level during VR exposure, time spent in VR, number of VR sessions completed) will be collected during the study to model missing data. SPSS version 21 will be used for the analyses. A *p* value < 0.05 will be considered to indicate statistical significance. All design, implementation, and reporting will be carried out in accordance with Consolidated Standards of Reporting Trials (CONSORT) and Standard Protocol Items: Recommendations for Interventional Trials (SPIRIT) guidelines (Additional file 1) [48–50].

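### The heterogeneity sentence names subgroup estimates but no test of whether the effect differs; an arm-by-baseline AQ interaction, with baseline continuous, would be better

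*Protocol article*

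**What the plan says.** The Statistical analyses section has one sentence on effect heterogeneity: "Potential heterogeneity will be addressed by estimating treatment effects for subgroups (e.g., based on pre-scores". It gives no number of subgroups and no cut-point, and baseline score is only an example. No interaction term or other test of a difference between effects appears anywhere in the article.

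The same section says that the intention-to-treat and per-protocol analyses use regression, with standardized effect sizes and confidence intervals. It sets one general criterion, a p "value < 0.05 will be considered to indicate statistical significance", with no separate rule for subgroups.

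The Sample size section plans for the overall comparison only. It uses a "standardized effect size (Cohen’s d) of 0.50 (two-sided), an alpha of 0.05" and power "of 0.80, we need 64 participants in each condition (128 participants in total". It then adds: "With an anticipated dropout of 40%, this requires a total target sample size of 180 participants". Randomization is "at an allocation ratio 1:1", which gives 90 per arm.

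**The concern.** Heterogeneity is a question about the difference between effects. An estimate in each subgroup describes each effect but does not give the size or the uncertainty of the difference. With a sample sized for the overall effect, each subgroup has well under 80% power at the planning value. One subgroup can then easily reach significance while another does not, even when the true effect is the same in both.

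The practical stake is a possible claim that a self-guided app works only in milder, or only in more severe, acrophobia. Such a claim could shape who is offered it. In addition, cutting a continuous baseline score into groups makes a real gradient harder to detect.

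**Working it through.** **Inputs from the article:** d = 0.50, two-sided alpha 0.05, 64 evaluable per arm, 90 randomized per arm, 40% dropout, and earlier effect sizes of 0.79-1.42. **Assumptions that are not in the article:** two subgroups, equal halves unless stated, outcome SD 1, and a reading in which each half is called significant or not at 0.05.

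**1. The plan's own figure.** With n = 64 per arm the noncentrality is d·√(n/2) = 0.50 × √32 = 2.83 on 126 degrees of freedom. The noncentral t gives power 0.801, so 64 per arm reproduces.

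**2. Analysed numbers.** Three cases are carried: 54 per arm (90 × 0.60), 64 per arm (the stated evaluable number) and 90 per arm (all outcomes observed or imputed).

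**3. Discordant halves under a uniform effect.** Let p be the noncentral-t power in one half. Then P(exactly one half significant) = 2p(1 − p).

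| Per arm (per half) | p at d = 0.50 | 2p(1 − p) | p at d = 0.79 | 2p(1 − p) |
|---|---|---|---|---|
| 54 (27) | 0.438 | 0.49 | 0.813 | 0.30 |
| 64 (32) | 0.504 | 0.50 | 0.875 | 0.22 |
| 90 (45) | 0.650 | 0.455 | 0.960 | 0.08 |

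At d = 1.42 the rate is about 0. With unequal splits (one third or one quarter in the smaller group) and d = 0.50 it is 0.51-0.59.

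**4. Baseline adjustment.** With baseline-outcome correlation r, the adjusted standardized effect is d/√(1 − r²). At r = 0.5 this is 0.50/√0.75 = 0.577. Power per half is then 0.549, 0.623 and 0.773, and discordance is 0.495, 0.470 and 0.351 at 54, 64 and 90 per arm. At r = 0.7 discordance is 0.41, 0.335 and 0.17.

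Splitting on the baseline itself also trims outcome variance within each half. Simulated rates at r = 0.5 without adjustment were 0.49, 0.48 and 0.40 (4,000 trials per setting).

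**5. Interaction test under the same uniform effect.** In the same simulations, with baseline either split at the median or kept continuous, the test rejected in 4.3% to 5.9% of trials.

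**6. Power of the interaction.** For a difference of 0.5 SD between equal halves, the standard error is √(4/(N/2)), with N per arm.
- N = 64: √(4/32) = 0.354; Φ(0.5/0.354 − 1.96) = 0.29.
- N = 90: √(4/45) = 0.298; Φ(0.5/0.298 − 1.96) = 0.39.

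**7. Loss from grouping.** This is one illustrative scenario: a true gradient of 0.4 SD per SD of baseline, with a baseline-outcome slope of 0.5. Simulated interaction power was 0.64 with continuous baseline against 0.39 with a median split at 54 per arm, and 0.85 against 0.58 at 90 per arm. The gradient is an assumption, so only the direction of the comparison carries weight.

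**The case against.** A reader might infer that the trial will judge heterogeneity by comparing significance between subgroups, in place of an interaction test, and would therefore misreport a uniform effect about half the time. The article does not support that. It does not say that the subgroup effects come from separate models or that their p-values will be compared. The 0.05 threshold is general and not a rule for heterogeneity, and confidence intervals are promised as well. Subgroup effects can be taken from a regression with an interaction term, so the sentence is compatible with good practice. The article is also condensed: cut-points and model terms are commonly left to an analysis plan, which is not shown here.

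The error rate is conditional too. The article calls its d = 0.50 conservative, and at the lowest earlier effect that it cites (0.79) discordance is 0.30 or less in equal halves. Strong baseline adjustment lowers it further in the larger samples. No primary conclusion depends on the heterogeneity analysis.

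All of that stands, and it sets the low priority. It does not remove the point. The article is not silent on method: it says how heterogeneity will be addressed, and the method it names does not by itself measure a difference between effects.

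**Conclusion.** The point holds in a limited form. The stated approach, subgroup estimates, does not measure whether the effect differs, and a better analysis is available from data already collected.

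If the subgroup results were read by significance, which is an inference and not a stated rule, two equal halves would disagree as follows under a uniform effect:
- about 45-50% at d = 0.50, unadjusted, with 54 to 90 per arm;
- about 35-50% at d = 0.50 with an assumed baseline-outcome correlation of 0.5 used for adjustment;
- 8-30% at d = 0.79, unadjusted.

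An interaction test would err about 5% of the time. A flat statement of half the time is not supported, because it needs the planning effect, a two-group split, the significance reading and little gain from adjustment. The interaction test also has limits: at 29-39% power for a 0.5 SD difference between halves, a non-significant result says little. The primary intention-to-treat result is unaffected.

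**What to change.** Replace the sentence on heterogeneity with wording such as: *Heterogeneity by baseline severity is tested with an arm by baseline AQ interaction (baseline continuous and centred) in the intention-to-treat regression. The interaction estimate and its 95% confidence interval are reported, and effects at chosen baseline values are taken from that model. Subgroup effects are shown as description only and are not tested separately. Other baseline moderators are treated in the same way. Power for the interaction is low, so a non-significant interaction is not taken as evidence of a uniform effect.*

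Because the AQ has an anxiety and an avoidance subscale, the wording should also say which baseline score enters the model. If an analysis plan already contains this interaction, a reference to it is enough.

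The cost is a few sentences and one model term, with no new data and no change to the primary analysis. A linear interaction can miss a non-linear pattern, which is a reason to keep the descriptive subgroup estimates beside it.

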## Methods/design

### Study design

A RCT will be carried out, in which the efficacy and user-friendliness of a self-guided, 3-week, mobile-app-based VR self-guided treatment “0Phobia” will be evaluated. In total, 180 participants from the Dutch general population will be randomized to two conditions: the experimental condition (0Phobia; *n* = 90) and a waitlist condition (*n* = 90). Measures will be taken at baseline and directly after the intervention (post test). After post-test assessment, the waitlist group will be granted access to the intervention. The experimental condition will receive a final follow-up questionnaire 3 months after baseline (follow-up). All measures will be completed online. Two reminders will be send (one by email, one by telephone) if necessary. This study has received ethical approval by the Medical Ethics Committee of the VU University Medical Center (registration number 2016–563) (Trial registration: NTR 6442). Figure 1 presents the flowchart of the study.

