Aside from the 2D animated environment, the intervention consists of a gamified immersive VR environment. From module 3 onwards, participants start to practice with exposure in the virtual environment, parallel to completing the remaining modules. The virtual environment is a gamified theater setting and within the story of the game, the participant is replacing Louise as the theater manager (see Fig. 2). To prepare the theater for the night’s performance, participants need to complete a number of assignments in the theater. Each of these assignments involve different levels of exposure to heights (from standing on a small ladder to standing on a ledge high above the stage). By looking at assets located on the theater floor that need to be collected, participants are encouraged to look down and face their fears.

Aside from the virtual theater, 0Phobia also contains four 360° videos that are also watched with the VR goggles in which participants stand on the top of a high building, cross a high suspension bridge, sit on a rooftop with their legs dangling over the edge, or stand on a high crane. In conjunction, the various virtual environment and 360° videos cover the entire exposure spectrum, from very-low- to very-high-intensity exposure. Based on the fear levels and performance the user receives feedback. When users rate their fear levels using a stare function in VR below a score of 3 on a 10-point scale, an automated feedback pops up mentioning that they can continue to the next level. When users rate their anxiety level between 4 and 7, they are advised to practice the same level again. When rated an anxiety level between 8 to 10, they need to practice the same level again before commencing to the next level. Subjects can return to practicing in VR as often as they like and gradually expose themselves to different heights and fear intensities. Although the importance of exposure in VR is stressed out in the 2D animations and participants are encouraged to practice in VR, participants can skip VR exposure and proceed to the next module, because for some people, fear levels may still be too high. After evaluating their automatic anxiety evoking thoughts, they can practice in VR exposure. Only during the exposure sessions will participants use the cardboard goggles.

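### The per-protocol sets rest on a follow-up questionnaire and module completion that the waitlist arm cannot supply, so the secondary between-arm per-protocol comparison has no controls or is filtered in one arm only

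*Protocol article*

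**What the plan says.** The Statistical analyses section names two per-protocol sets: "1) those who returned the post-test and follow-up questionnaires (completers) and (2) those who completed 50% or more of the treatment modules". In full, the second is "2) those who completed 50% or more of the treatment modules and returned the questionnaires (adherent completers"). Neither is worded differently for the waitlist. The section then announces comparisons both between and within groups. Its closing paragraph applies regression, Cohen's d and confidence intervals to the per-protocol analysis in the same way as to intention-to-treat. It also states that intention-to-treat is the primary analysis.

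The assessment schedule is given twice. Study design says "The experimental condition will receive a final follow-up questionnaire 3 months after baseline (follow-up"), and Procedure repeats it: "After 3 months, participants in the experimental condition are asked to fill in the follow-up questionnaire". On access to the app, Study design says "After post-test assessment, the waitlist group will be granted access to the intervention". The abstract lists the follow-up without naming arms, but no section gives the waitlist a follow-up questionnaire.

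**The concern.** A per-protocol set supports a comparison of arms only if people in both arms can enter it by a comparable rule. Here both entry conditions depend on things that only the app arm has when the arms are compared. The analyst must then either report a per-protocol analysis without controls or improvise a control set after the data are in.

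The obvious improvisation is to waive the conditions for the waitlist. That compares app users who persisted with controls who were not asked to persist. The first set has a further weakness: the only controlled comparison is at post test, after a 3-week intervention, whereas follow-up return is observed 3 months after baseline. Membership would therefore depend on an event that comes after the outcome and may be influenced by it.

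At stake is the credibility of a secondary effect size that will be reported beside the intention-to-treat result.

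**Working it through.** **Step 1: apply the definitions to the schedule.**

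| Condition | Experimental arm (n = 90) | Waitlist (n = 90) |
|---|---|---|
| Sent the post test | yes | yes |
| Sent the 3-month follow-up | yes | no |
| Has modules before post test | yes | no |
| Can be a completer as written | yes | no: 0 of 90 |
| Can be an adherent completer as written | yes | no: 0 of 90 |

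This step needs no assumption. For follow-up return the exclusion is absolute. For modules it holds up to the post test: the waitlist could complete modules afterwards, but too late to define a set for the controlled comparison, and the second set also needs the returned questionnaires.

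**Step 2: the yardstick.** Sample size plans for d = 0.50, two-sided alpha 0.05 and power 0.80, with 64 per arm. This reproduces: the two-sample t-test needs 63.8 per arm, and 64 gives power 0.801. The per-protocol sets play no part in that calculation; d = 0.50 serves only as a scale for Step 3.

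**Step 3: size of the shift if the rule is waived for the waitlist.** Suppose a fraction p of the app arm qualifies and the latent tendency to qualify correlates r with a better outcome. With no treatment effect, the expected difference in SD units is

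bias = r × φ(z_p) / p,

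where φ is the standard normal density and z_p the normal quantile of p.

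- p = 0.60 is an assumption taken from the 40% dropout in Sample size: 1 − 0.40 = 0.60, or 54 of 90. The document does not say that this dropout figure describes follow-up return or module completion.
- r is not in the document, so a range is shown.
- φ(z_0.60) = φ(0.253) = 0.386, and 0.386 / 0.60 = 0.644.

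| r | Bias (SD) at p = 0.60 | Rejection by nominal 5% test |
|---|---|---|
| 0.1 | 0.1 × 0.644 = 0.06 | about 7% |
| 0.2 | 0.2 × 0.644 = 0.13 | about 12% |
| 0.3 | 0.3 × 0.644 = 0.19 | about 20% |
| 0.4 | 0.4 × 0.644 = 0.26 | not simulated |
| 0.5 | 0.5 × 0.644 = 0.32 | about 49% |

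The rejection rates come from 4000 simulated trials per setting, with 90 per arm, no true effect and an unselected waitlist.

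**Step 4: the same filter in both arms.** When both arms were selected by one rule with the same correlation, rejection stayed at about 4% to 5%. The problem is the asymmetry of the filter.

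**The case against.** *The sets may not be meant for comparing arms.* The sentence about comparing groups directly follows the one naming the two per-protocol groups, so the groups could be completers and adherent completers. The Background also hypothesises change from baseline within the experimental arm, for which requiring both questionnaires is coherent. This reading is possible but awkward, because adherent completers appear to be a subset of completers. It would also leave the per-protocol analysis with no controlled estimate, although effect sizes are planned for it as for intention-to-treat.

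*A condensed article may mean the questionnaires each arm was sent.* The waitlist set would then be its post-test returners, and part of the selection might cancel. That is fair, but the extra follow-up and module filters would still fall on one arm. The point concerns stated definitions that conflict with the stated schedule, not missing detail.

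*Lee bounds are planned.* They address non-random missing outcomes and so bear on questionnaire non-return. They are not stated to cover exclusion by module count.

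*Stronger readings.* A reader might infer any of the following, and the document supports none of them.

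- That the trial's main result is compromised. Intention-to-treat is primary, and the sample size does not rest on these sets.
- That the per-protocol effect is certain to be inflated, by 0.19 to 0.39 SD. Those figures need 40% of the app arm to qualify (φ(z_0.40) / 0.40 = 0.966, times r = 0.2 to 0.4). Neither that rate nor the correlations are in the document, and the direction is assumed too.
- That the 50% threshold is invalid because "participants can skip VR exposure and proceed to the next module". The intervention is a package that includes psychoeducation and cognitive techniques, so a module-based threshold is a legitimate choice, and VR use is examined separately through usage intensity.
- That the planned mechanism analyses are an error because their variables exist only in app users. That is inherent in such variables; relabelling the analyses is a matter of preference.

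**Conclusion.** The point holds as a secondary-level defect that is wrong as written. Both per-protocol definitions conflict with the document's own schedule: applied literally, the control side of the comparison is 0 of 90. Applied to the app arm alone, they break the comparability that randomisation gave.

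The empty control set follows from the text without assumptions. The illustrative 0.13 to 0.26 SD rests on four: 60% of the app arm qualifying, a correlation of 0.2 to 0.4, selection towards better outcomes, and an unselected waitlist. The true size and direction are unknown, but a shift of that order would be roughly a quarter to a half of the planned 0.50 (0.13 / 0.50 = 0.26; 0.26 / 0.50 = 0.52). The primary intention-to-treat analysis is unaffected.

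**What to change.** 1. For every between-arm per-protocol comparison, define completers in both arms by return of the post-test questionnaire only. One rule for both arms removes the built-in asymmetry. Return may still depend on arm, so the planned attrition checks remain useful.
2. Use the follow-up and 50%-of-modules criteria only for analyses within the experimental arm, and report these as non-randomised.
3. If a between-arm adherence effect is wanted, estimate a complier-average effect with randomisation as the instrument and uptake defined as any app use. The waitlist has no access before post test, so non-uptake is one-sided. State the exclusion restriction: assignment must not affect outcome in people who never use the app, even though they receive the goggles and weekly emails. A higher threshold, such as half the modules, would be less credible because partly treated people would count as untreated and their benefit would be credited to the adherent. The estimate is the intention-to-treat effect divided by the uptake fraction, so it need not be small: an effect of 0.30 SD with 40% counted as adherent would become 0.30 / 0.40 = 0.75 SD.

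Cost: a few sentences for items 1 and 2, and one further regression, with lower precision, if item 3 is adopted. No new questionnaires are needed. For item 3 the team should confirm that the app record shows who has used it at all.
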